#### Pre-specified subgroup analysis

To examine whether the effect of decision-support is consistent across specific subgroups of babies, the following subgroup analyses will be undertaken, using the statistical test of interaction:Singletons versus twinsSuspected IUGR at labour onset versus no growth restrictionBMI group for the subset of women with this recorded: underweight (<18.5); normal (18.5–24.9); overweight (25–29.9); obese (>30); unrecordedCentre

#### Economic evaluation

All analyses will be conducted on the basis of intention-to-treat. As the data for costs are likely to be skewed, we shall use non-parametric bootstrap estimation to derive 95 % confidence intervals for mean cost-differences between the trial groups [41]. Non-parametric bootstrap methods will also be used to calculate 95 % confidence intervals for incremental cost-effectiveness ratios. In the absence of stochastic data for all variables, a series of multi-way sensitivity analyses will be undertaken, to explore the implications of uncertainty on the base-case incremental cost-effectiveness ratios. In addition, cost-effectiveness acceptability curves will be constructed using the net-benefits approach [42].

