#### Health economics

A prospective economic evaluation will be conducted alongside the trial, with the aim of estimating the cost-effectiveness of the intelligent decision-support software. The economic evaluation will be conducted from a health-service perspective. Information on resource utilisation will be collected through the Guardian® system and hospital-patient administration and maternity information systems. Observational research methods may be used to collect additional costs in intrapartum, postpartum or neonatal care. Current UK unit costs will be applied to each resource item to value total resource use in each arm of the trial. A per diem cost for each level of intrapartum, postnatal and neonatal care will be calculated using NHS reference costs where appropriate, or by sending a detailed questionnaire to the finance department of each centre participating in the trial. The unit costs of clinical events that are unique to this trial will be derived from the hospital accounts of the centres participating in the trial, although primary research may also be required. An incremental cost-effectiveness analysis will be performed and primarily expressed in terms of an incremental cost per poor-perinatal-outcome prevented. The primary outcomes of the trial are likely to have longer-term consequences in terms of health status and health-service utilisation over the mother’s and infant’s lifetime. Consequently, two long term economic evaluations are planned, which in the first instance will estimate the cost-effectiveness of the decision-support software when surviving children reach 2 years of age, and in the second instance will incorporate the lifetime cost and health consequences of the mother and child. To inform the long-term economic evaluations, a subsample of 700 healthy infants selected within the first year of recruitment and all babies with the primary trial outcome who survive to hospital discharge and agree to follow-up will be followed up until 2 years of age or until the end of the trial, whichever comes first. Economic questionnaires completed when the infant reaches 1 and 2 years of age will document the health and social care use of the child and mother. Cost data collected until hospital discharge and from the parental questionnaires will be combined with the PARCA-R composite score at 2 years of age to inform the incremental cost per disability free life years gained when surviving children reach 2 years of age [32]. Given the potential long-term sequelae, these data will then be used to extrapolate long-term outcomes and costs over the child’s lifetime, identifying future health care costs and the health status of mothers and infants from literature as well as the application of decision-analytic or markov methods to synthesise information from different sources. This will require modeling longer-term health-service utilisation from literature and also estimating the potential medico-legal claims that result from adverse events during the intrapartum and neonatal periods.

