#### Effect size

The effect size which can be detected with 46,000 women (23,000 in each group), assuming a 5 % level of significance and 90 % power, is a 50 % reduction in poor neonatal outcome rate from 3 to 1.5 per 1000. We have approximated the number of women recruited with the number of infants born, even though women with a twin pregnancy are eligible to join the trial. Approximately 1 in 80 pregnancies are twin pregnancies, however, a proportion of these births will occur before 35 weeks’ gestation and a large proportion of the term births will be by elective caesarean section. We therefore estimate that fewer than 1 % of all births in the study will be twins. In a study of 164 preterm infants [29], the mean (SD) PARCA-R composite score at 2 years was 80 (SD 33) and the mean Mental Development Index (Bayley Scales of Infant Development II) was approximately half a standard deviation below the standardised mean of 100. If we assume that a normal group of term infants would have a PARCA-R composite score half a standard deviation above this sample of preterm infants, then we can estimate a mean (SD) 2 year score of 96 (SD33). Based on this estimate, a follow up sample of size 7000 (3500 per arm) in the INFANT study would have over 90 % power to detect a difference of 3 points in the PARCA-R component score with a two-sided 5 % significance level. The incidence of severe metabolic acidosis (cord-artery pH <7.05) is 10 per 1000 [36–39]. Our proposed sample size will therefore enable us to detect a 28 % relative risk reduction in incidence with over 80 % power in those babies who have their cord artery pH measured.

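### The planned bootstrap confidence interval for the cost-effectiveness ratio cannot be interpreted when the effect on the primary outcome is not clearly different from zero

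*Protocol article*

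**What the plan says.** The Health economics section of the protocol article says the incremental cost-effectiveness analysis will be "primarily expressed in terms of an incremental cost per poor-perinatal-outcome prevented". The denominator of the main ratio is therefore the between-arm difference in the primary short-term outcome.

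The Economic evaluation section names three expressions of sampling uncertainty:

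- for costs, "we shall use non-parametric bootstrap estimation to derive 95 % confidence intervals for mean cost-differences between the trial groups";
- for the ratio, "Non-parametric bootstrap methods will also be used to calculate 95 % confidence intervals for incremental cost-effectiveness ratios";
- and then, "In addition, cost-effectiveness acceptability curves will be constructed using the net-benefits approach".

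The interval for the ratio carries no condition on the size or certainty of the effect. The type of bootstrap interval is not named.

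The precision of the denominator follows from the Effect size section: "The effect size which can be detected with 46,000 women (23,000 in each group"), "assuming a 5 % level of significance and 90 % power", for "a 50 % reduction in poor neonatal outcome rate from 3 to 1.5 per 1000".

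**The concern.** A ratio of two differences behaves well only while its denominator stays away from zero. Write ΔC for the extra cost with decision support and ΔE for the poor outcomes prevented per woman. If the data are compatible with ΔE = 0, two things go wrong.

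- **Different results share one ratio.** Take ΔE = 0.0006 (the effect at relative risk 0.8) and an illustrative £20. Dearer and better gives 20 / 0.0006 = £33,333. Cheaper and worse gives −20 / −0.0006, again £33,333. Cheaper and better, and dearer and worse, both give −£33,333.
- **The order breaks at zero.** For a positive cost difference, the ratio runs to plus infinity as ΔE falls to zero from above, and to minus infinity as it rises to zero from below. Replicates that are neighbours on the cost-effectiveness plane land at opposite ends of the ordered list.

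Limits cut from such a list are still two numbers, but they do not bound the cost of preventing one poor outcome. At stake is how the main economic result is read: a negative limit could be taken as evidence of cost saving when it comes from replicates in which decision support costs more and does worse.

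**Working it through.** **1. The plan's own figure.** With 3 versus 1.5 per 1000, 23,000 per arm and a 5 % level (two-sided assumed; the protocol does not say for this outcome), power is 92.4 % without and 90.9 % with continuity correction. The total for 90 % power is 41,932 without and 44,558 with correction. The stated 46,000 is slightly conservative and is not disputed. It fixes the precision of the denominator.

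**2. How often the effect interval includes zero.** Inputs: control rate p0 = 0.003 and n = 23,000 per arm (Effect size); the relative risk (RR) is assumed.

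- p1 = p0 × RR; ΔE = p0 − p1
- SE = √[(p0(1 − p0) + p1(1 − p1)) / n]; z = ΔE / SE
- P(interval includes 0) = Φ(1.96 − z) − Φ(−1.96 − z)
- share of replicates with ΔE ≤ 0, when the observed effect equals the expected one = Φ(−z)

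Example, RR 0.75: ΔE = 0.00075; SE = √[(0.002991 + 0.002245) / 23,000] = 0.000477; z = 1.57; P = Φ(0.39) − Φ(−3.53) = 0.65.

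| RR | ΔE per 1000 | SE per 1000 | z | P(interval includes 0) | Share with ΔE ≤ 0 |
|---|---|---|---|---|---|
| 0.5 | 1.50 | 0.442 | 3.40 | 7.6 % | 0.03 % |
| 0.75 | 0.75 | 0.477 | 1.57 | 65 % | 5.8 % |
| 0.8 | 0.60 | 0.484 | 1.24 | 76 % | 10.8 % |
| 0.9 | 0.30 | 0.497 | 0.60 | 91 % | 27 % |

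The section on the incidence of the primary outcome calls 3 per 1000 cautious. At 6 per 1000, the highest rate in Table 2, with the same n and RR 0.75: ΔE = 0.0015, SE = 0.000674, z = 2.23, and P = Φ(−0.27) − Φ(−4.19) = about 40 %. The problem shrinks but remains.

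**3. Where the replicates fall.** The protocol gives no costs. Assume a cost SD of £2,000, so that SE(ΔC) = 2,000 × √(2 / 23,000) = £18.65, and cost independent of effect. With the observed effect and cost set at their expected values:

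| RR | ΔC | Dearer, better | Cheaper, better | Dearer, worse | Cheaper, worse | 2.5 % and 97.5 % points of ΔC/ΔE |
|---|---|---|---|---|---|---|
| 0.5 | £50 | 99.6 % | 0.4 % | 0.04 % | 0 % | £8,356 to £90,653 |
| 0.8 | £20 | 76 % | 12 % | 10 % | 2 % | −£239,830 to £512,593 |
| 0.8 | £50 | 88 % | 0.3 % | 11.5 % | 0.04 % | −£491,724 to £1,216,121 |

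In the last row the extra cost is fairly certain (50 / 18.65 = 2.7 standard errors) and almost no replicate is cheaper and better. The negative lower limit therefore comes almost wholly from replicates that are dearer and worse. In the middle row the sign of the cost difference is uncertain as well, and dominant and dominated replicates are mixed.

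**4. Coverage.** Percentile limits, cost SD £2,000, mean cost difference £20, £50 or £100; 3,000 simulated trials of 1,000 replicates per setting:

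| RR | Coverage of the true ratio |
|---|---|
| 0.5 | 0.95–0.97 |
| 0.8 | 0.97–0.98 |
| 0.9 | about 0.96 |
| 0.95 | 0.91–0.93 |
| 0.98 | 0.78–0.82 |
| 1.02 | 0.36–0.71 |

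At RR 1.0 the ratio is undefined. Across other cost assumptions coverage stayed at about 0.95–0.99 down to RR 0.9, and ranged from about 0.62 to 0.97 at RR 0.98.

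**The case against.** The strongest case against the point has four parts.

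- **The method is only sketched.** The article names a non-parametric bootstrap, not percentile limits, and an analysis plan that is not shown may set the details. This stands for the coverage figures, which depend on an assumed interval type. It does not remove the point: the interval is a stated, unconditional output, and any interval built by ordering the resampled ratios meets the same break at zero.
- **The usual remedy is already planned.** Under Economic evaluation, "cost-effectiveness acceptability curves will be constructed using the net-benefits approach". Net benefit has no ratio denominator, and a reader will also see intervals for the cost difference and, from the primary analysis, for the risk ratio. This stands and is the main reason the point is minor. These displays sit beside the ratio's interval, however, and do not make it readable.
- **Coverage mostly holds.** A reader might infer that the interval works only if the full 50 % reduction is found, or that it generally loses its 95 % property. The figures do not support either: under the assumed costs coverage is near nominal down to RR 0.9.
- **The costs are invented.** True, and cost was taken as independent of effect although the composite includes neonatal admissions, which generate cost. The table in step 2 needs no cost input.

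**Conclusion.** The point holds as a minor one. The plan fixes an interval for the cost-effectiveness ratio whatever the effect. Unless the effect is near the one postulated, most trials of this size would compute that interval from ratios that cross a zero denominator: about 65 % of trials at RR 0.75 and 91 % at RR 0.9, against about 8 % at RR 0.5. These figures rest on the protocol's control rate and sample size, an assumed relative risk and a normal approximation. A higher control rate lowers them.

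At moderate effects the failure is one of interpretation. Failure of coverage is confined to effects close to none, from about RR 0.95 towards 1, and that statement depends on percentile limits and assumed costs.

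Three further inferences go beyond the documents:

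- A weak effect alone does not mix dominant with dominated results. That also needs a cost difference of uncertain sign.
- The economic conclusion does not rest on this interval alone, given the curves and cost-difference intervals.
- The wording would also cover the two-year ratio, cost per disability-free life year, but that has a different denominator and follow-up sample, and the article gives no figures from which to size the problem there.

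The primary clinical analysis is unaffected.

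**What to change.** In the Economic evaluation section:

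1. Make a bootstrap 95 % interval for incremental net benefit, λ × ΔE − ΔC, the main statement of uncertainty, over the willingness-to-pay values λ already needed for the acceptability curves.
2. Show the bootstrap replicates on the cost-effectiveness plane.
3. Give a confidence interval for the ratio only when the replicates do not cross a zero effect difference to a material degree, for example when the 95 % interval for that difference excludes zero.
4. Otherwise report the cost and effect differences with their intervals, the plane and the net-benefit results. Give no interval for the ratio, and no ratio point estimate without that qualification, so that the rule does not leave a bare figure where uncertainty is greatest.

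The rule should be set before results are known. The cost is wording only, since the same replicates serve every display. The downside is that there is no single range around the ratio when the effect is uncertain.

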#### Loss to follow-up

Loss to follow-up for the short term primary outcome will be negligible, as most of this information is collected before the woman leaves the delivery room where she has been recruited. For neonatal outcomes of the small number of babies admitted to the neonatal unit, we will collect data for all of these babies through the research midwives employed by the study in the participating centres. For the rare instances where babies are transferred out of the recruiting hospital to another hospital for specialist care, data will be collected from all the hospitals providing care for that child prior to discharge home or death. At the time of entry to the study all women will be asked for permission for their contact details to be downloaded to the trial co-ordinating centre along with their clinical details from the Guardian® system. Families selected for follow-up at 2 years will be contacted by post 8 weeks after birth and informed that they have been selected for the follow-up study. Contact with families who agree to take part will be maintained during the period between birth and the follow-up assessment by sending a birthday card each year along with a FREEPOST change-of-address card to facilitate communication with UCL CTU about updated contact details.

### Trial management

#### Project timetable and milestones

The aim is to randomise 46,000 women to the trial over 36 months. Approximately 320 women per week will therefore need to be recruited. A conservative estimate of the proportion of women who receive EFM in labour and are therefore eligible for trial entry is 60 %.

#### Arrangements for research ethics committee approval

The Investigators will ensure that this study is conducted in accordance with the principles of the current revision of the Declaration of Helsinki (last amended October 2008) and with relevant regulations and with the MRC GCP guidelines which are based on ICH Guidelines for GCP (CPMP/ICH/135/95) July 1996. The trial has National Research Ethics Service – Northern and Yorkshire Research Ethics Committee approval—and local approvals from all the participating centres.

#### Research governance

The sponsor of the trial is UCL. The trial will be run on a day-to-day basis by the UCL CTU Project Management Group. This group reports to the Trial Steering Committee which is responsible to the Research Sponsor (UCL). At each participating centre, local Principal Investigators will report to the Project Management Group via the project funded staff based at the UCL CTU.

#### Insurance

NHS indemnity operates in respect of the clinical treatment being provided. In addition, UCL has appropriate insurance-related arrangements in place in respect of the University’s role as Research Sponsor of this study.

#### Trial steering committee

The trial will be supervised by an independent Trial Steering Committee (TSC). The precise terms of reference for the TSC were agreed at their first meeting. A TSC Charter similar to that used by the DMC (see below) has been completed.

#### Data monitoring committee

An independent Data Monitoring Committee (DMC) has been established for the trial. This is independent of the trial organisers and will meet yearly. The terms of reference for the DMC were agreed at their first meeting. A DMC charter has been completed following the recommendations of the DAMOCLES Study [43].

During the period of recruitment to the trial, interim analyses will be supplied, in strict confidence, to the DMC, together with any other analyses the DMC may request. The data will be supplied to the Chair of the DMC as frequently as they request. Meetings of the committee will be arranged periodically, as considered appropriate by the Chair. In the light of interim data, and other evidence from relevant studies (including updated overviews of the relevant randomised controlled trials), the DMC will inform the TSC, if in their view there is proof beyond reasonable doubt that the data indicate that any part of the protocol under investigation is either clearly indicated or contra-indicated, either for all women or for a particular subgroup of trial participants. A decision to inform the TSC will in part be based on statistical considerations. Appropriate criteria for proof beyond reasonable doubt cannot be specified precisely. A difference of at least 3 standard errors in the interim analysis of a major endpoint may be needed to justify halting, or modifying, such a study prematurely. If this criterion were to be adopted by the DMC, it would have the practical advantage that the exact number of interim analyses would be of little importance, and so no fixed schedule is proposed [44]. Unless modification or cessation of the protocol is recommended by the DMC, the TSC, collaborators and administrative staff (except those who supply the confidential information) will remain blind to the results of the interim analysis. Collaborators and all others associated with the study may write through the trial office to the DMC, to draw attention to any concern they may have about the possibility of harm arising from the treatment under study, or about any other matters that may be relevant.

#### Publication policy

The Chief Investigator will co-ordinate dissemination of data from this study. All publications using data from this study to undertake original analyses will be submitted to the TSC for review before release. To safeguard the scientific integrity of the trial, data from this study will not be presented in public before the main results are published without the prior consent of the TSC. The success of the trial depends on a large number of midwives and obstetricians. For this reason, chief credit for the results will not be given to the committees or central organisers, but to all who have collaborated and participated in the study. Acknowledgement will include all local co-ordinators and collaborators, members of the trial committees, the Trial Co-ordinating Centre and trial staff. Authorship at the head of the primary results paper will take the form “The INFANT Collaborative Group”. This avoids giving undue prominence to any individual. All contributors to the study will be listed at the end of the report, with their contribution to the study identified. Those responsible for other publications reporting specific aspects of the study may wish to utilise a different authorship model, such as “[name], [name] and [name] on behalf of the INFANT Collaborative Group”. Decisions about authorship of additional papers will be discussed and agreed by the trial investigators and the TSC. The women participating in the trial will be sent a summary of the final results of the study, which will contain a reference to the full paper. A copy of the journal article will be available on request.

#### Time period for retention of relevant trial documentation

The policy of UCL CTU is to retain documentation from all its research indefinitely as it is always ‘fit for purpose’. Clinical research in the perinatal period, particularly in relation to new interventions, has the potential to lead to a wide range of unanticipated effects. Thalidomide and diethylstilboestrol are classic examples. Although such effects are most likely with new medicines, we cannot be certain that there will be no long-term consequences of this new technology and that it may become necessary, in the public interest, to undertake long-term follow-up of this cohort of recruited women and children in the future. Any further follow-up will require the necessary approvals before it can go ahead.

## Discussion

This large randomised controlled trial will evaluate whether this intelligent system to support decision making in the management of labour using the cardiotocograph improves perinatal outcome for babies and mothers. By accurately identifying abnormal fetal heart rate patterns associated with perinatal compromise, the system has the potential to refine the use of intrapartum interventions such as emergency caesarean section and instrumental delivery for presumed fetal distress. By correctly identifing the distressed fetus, intervention can be offered in a timely way to improve outcomes, but it may also provide reassurance that the fetus is not compromised and the technology therefore has the potential to decrease unnecessary intervention.

The results of this trial will have importance for pregnant women and for their health professionals.

All changes to this protocol are listed in Table 3.

**Table 3 Tab3:** Document history

*Version*	*Date*	*Comments*
*1.*	*May 2009*	*Completion of first version.*
*2.*	*Aug 2009*	*Minor edits to text throughout.*
*3.*	*Oct 2009*	*Minor edits to formatting throughout.*
*4.*	*April 2010*	*Minor edits to text.*
*5.*	*May 2011*	*Minor edits to text.*
*6.*	*July 2011*	*Minor edits to text.*
*7.*	*Feb 2012*	*Minor edits to text.*
*8.*	*Mar 2012*	*Minor edits to text.*
*9.*	*May 2012*	*Change of sponsor from University of Oxford to University College London*
*10.*	*Sept 2012*	*Updated contact details for trial staff*
*11.*	*Oct 2012*	*Change wording of primary outcome definition from ‘NICU’ to ‘neonatal unit’.*
*12.*	*Jan 2014*	*Inclusion of primary outcome review process, changes to introduction to match protocol v1, grouping of secondary outcomes as either major diasability or non-major disability*
